### Statistical analysis

Differences in the primary outcomes will be analyzed using the “intention-to-treat” principle. The mean decisional conflict score and the mean knowledge score will be compared, using the t-test, to the respective means in the control group. Comparing the actual mode of delivery in the intervention and control groups will be based on hospital maternity records and differences will be tested by the Chi square test. We will calculate the Pearson correlation coefficient between the score of decisional conflict and the mode of delivery.

We will handle missing data by a multiple imputation approach. The multiple imputation procedure replaces each missing value with a set of acceptable values that represent the uncertainty about the right value to impute. These multiply imputed data sets are then analyzed by using standard procedures for complete data and then the results from these analyses are combined.

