### Study design

This study follows is a randomized controlled trial design. Subjects (pregnant women) are the unit of randomization; they are randomly allocated to each arm of the study. Both the intervention and control group will receive usual care, but the intervention group will also receive the CDA. An independent researcher will centrally perform the randomization by using the computer program on www.randomization.com. Block randomization will be applied to ensure equal group sizes within each center. Because the study is not blinded, we use blocked randomization with randomly selected block sizes of two and four. For each center, the independent researcher will prepare opaque, sequentially numbered, and sealed coded envelopes, with a note for either the decision aid use or not. At each center, the clinic secretary will check eligibility of each pregnant woman visiting the clinic and, if eligible, will provide her with an explanation of the aims and scope of the study and will orally invite her to participate in the study. If the invitee accepts the invitation, then she will be asked to sign the informed consent form. Then the secretary writes the woman’s name and phone number on the next closed envelope. At the end of the day, all envelopes, unopened as of yet, are collected by a research assistant. At the university, this researcher assistant opens the envelopes and allocates the participants of that day to the decision aid or control group. After group allocation, the research assistant will call the participants by phone. Those in the intervention arm will be invited to a software educational session (consisting of 10 women in total) and invited to fill in the paper questionnaires. Those in the control arm will be invited to only fill in the questionnaires. All participants (in the intervention and control arms) will be invited to fill in the questionnaires again two weeks before the expected date of delivery. Blinding of researchers and women is not practical in this study, but the gynecologists are unaware of the patient allocations.

The duration of the intervention is considered from recruitment to the time of delivery. The evaluation of the intervention will be performed at 38 weeks of gestation and before delivery. We will report all cases due to premature delivery.

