### Data collection

Women are asked to complete two questionnaires: the first one upon entering the study and the second one during their 38^th^ week of gestation. Other information (related to women's health status) will be collected from pregnant women’s medical records in the hospitals and clinics.

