### Outcome

The two primary outcomes for the study are the mean of overall decisional conflict and knowledge scores. The decisional conflict will be measured by O’Connor Decisional Conflict Scale (DCS) [25, 30]. The DCS subscales are secondary outcomes, and they will be compared between the two groups of women. The results of this study will show the specific three affected subscales in the pregnant women's decisional conflict scale. Subscale 1 addresses the uncertainty about choosing among alternatives. Subscale 2 addresses factors contributing to uncertainty, including a - feeling uninformed about the alternatives, benefits and risks; b - being unclear about personal value; c - feeling unsupported in making a choice or pressured to choose on course of action. Finally, subscale 3 addresses the perceived effectiveness of the decision [30].

The DCS scale is assessed for validity and reliability using statistical tests, including factor analysis and Cronbach alpha test. A Persian version of the scale was used in 212 pregnant women in Mashhad, Iran.

Knowledge acquisition will be evaluated by 15 true/false questions that are provided by the researchers. The actual mode of delivery, which will be measured by data obtained from hospital records after the intervention. We will determine the studied pregnant women's decision on mode of delivery before and after intervention and compare the results with the actual delivery mode. We will not evaluate cases with emergency delivery but report on them in the two groups.

The acceptability of the CDA by the enrolled pregnant women in the intervention arm will be assessed by interviewing them and analyzing open-ended comments. Our participants' experiences regarding the use of the decision aids will be reported. Also we will discuss our experience with the CDA’s implementation.

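### The unadjusted t-test and chi-square ignore center, and a baseline score that could be used if it were collected before allocation; the cost is efficiency, not validity

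*Protocol article*

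**What the plan says.** The Outcome section of the protocol article defines the endpoints: "The two primary outcomes for the study are the mean of overall decisional conflict and knowledge scores". The Statistical analysis section fixes the test: "The mean decisional conflict score and the mean knowledge score will be compared, using the t-test, to the respective means in the control group". The same section tests delivery mode by chi-square. No baseline or center term is named for either analysis.

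Two features of the design bear on this.

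- **Center.** The Study design section states: "Block randomization will be applied to ensure equal group sizes within each center". The Abstract gives four centers, two private and two public.
- **Baseline.** The Data collection section says: "Women are asked to complete two questionnaires: the first one upon entering the study", with the second in week 38. The Study design section says that all participants "will be invited to fill in the questionnaires again two weeks before the expected date of delivery".

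The Study design section also sets the order of events: "After group allocation, the research assistant will call the participants by phone". In that call, intervention women are "invited to a software educational session (consisting of 10 women in total) and invited to fill in the paper questionnaires". Control women are invited only to the questionnaires.

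**The concern.** When allocation is balanced within center, differences between centers are removed from the treatment contrast. A test that ignores center leaves that variance in its standard error. If centers differ in outcome, the standard error is too large and the test rejects less often than its nominal 5% under the null. Differences are plausible here, because the centers are of two kinds and the Background links cesarean delivery with private hospitals.

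Baseline works differently. Leaving out a prognostic baseline score keeps the t-test at its nominal level but wastes information, so power is lower than the same women could provide. That matters because the sample size has little room for loss: the calculation below needs about 192 per arm, and 200 are planned.

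**Working it through.** **Inputs from the Sample size section.** DCS mean 33.6, SD 17.6, 200 per arm, 80% power, 5% type I error (two-sided taken).

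**Reading of the target.** The 400 reproduces approximately if the 15% is relative to the mean: 0.15 × 33.6 = 5.04 points. A literal 15 points on the scale would need only 22 per arm. I therefore use 5.04 throughout.

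**Step 1: the plan's own figure.** n per arm = 2 × 17.6² × (1.960 + 0.842)² / 5.04² ≈ 191.4, so 192 per arm and 384 in total, 4% below 400. At 200 per arm the standard error is 17.6 × √(2/200) = 1.76 and t-test power is 81.5%.

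**Step 2: effect of baseline adjustment on DCS.** Residual SD = 17.6 × √(1 − r²). The documents give no correlation r between baseline and follow-up, so r is an assumed range. The 170 per arm column assumes 15% loss and analysis of the women observed.

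| r | Residual SD | Power, 200 per arm | Power, 170 per arm |
|---|---|---|---|
| unadjusted | 17.60 | 81.5% | 74.9% |
| 0.3 | 16.79 | 85% | 79% |
| 0.5 | 15.24 | 91% | 86% |
| 0.7 | 12.57 | 98% | 96% |

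The test sentence does not say whether the week-38 score or the change from entry is compared; the unadjusted row takes the week-38 score. A change-score t-test has SD 17.6 × √(2(1 − r)), which at r = 0.3 is 20.82 and gives 67.7% power at 200 per arm (normal approximation). ANCOVA beats both for any r between 0 and 1. The article gives no SD or target difference for knowledge, so no power can be computed for that outcome.

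**Step 3: effect of ignoring center on the t-test.** If a share f of outcome variance lies between centers (assumed), the true standard error is √(1 − f) times the reported one, and the true type I error is 2[1 − Φ(1.96/√(1 − f))].

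| f | True type I error | Power without center | Power with center |
|---|---|---|---|
| 0 | 5.0% | 81.7% | 81.7% |
| 5% | 4.4% | 82.3% | 83.6% |
| 10% | 3.9% | 83.0% | 85.5% |
| 20% | 2.8% | 84.4% | 89.3% |

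(Powers here use the normal approximation, hence 81.7% rather than 81.5%.)

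A simulation with four centers of 100, r = 0.5 and f = 10% agrees. The t-test reports a mean standard error of 1.76 against a true 1.64, with type I error 3.7% and power 82.6%. A model with center and baseline gives 1.45 against 1.44, 4.9% and 93.3%.

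**Step 4: effect of ignoring center on the chi-square.** The cesarean rates are assumed. The variance ratio is the average within-type p(1 − p) divided by the overall p(1 − p).

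- 40% public, 64% private, equal numbers: (0.2400 + 0.2304)/2 = 0.2352; overall 0.52 × 0.48 = 0.2496; ratio 0.942. Type I error = 2[1 − Φ(1.96/√0.942)] ≈ 4.3%.
- 30% and 70%, equal numbers: 0.2100/0.2500 = 0.840; type I error ≈ 3.2%.
- Recruitment in proportion to the monthly volumes in the Setting section (about 1,700 public and 700 private; proportionality assumed): ratios 0.952 and 0.864; type I error ≈ 4.5% and 3.5%.

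**Step 5: is the baseline score usable as collected?** By the Study design section, envelopes are opened at the university, women are then phoned, and intervention women are asked to the software session and the questionnaires in one invitation. The first form therefore follows unblinded allocation and, in one arm, may be filled in at or after exposure to the decision aid. A score affected by the intervention is not a baseline, and adjusting for it could remove part of the treatment effect.

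**The case against.** The strongest objection is that nothing here is invalid. Under randomization the unadjusted t-test is unbiased, omitting baseline leaves its level at 5%, and omitting the stratifier can only push the error rate to the safe side. The planned test and planned sample size match each other. All of this stands. A reader might infer that the plan is biased, has an inflated error rate or misses its power target; the documents do not support any of these.

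The sizes also rest on assumptions: no correlation and no center differences are given. At r = 0.3 the gain is only 3 to 4 points, and at f = 5% the center term adds about 1 point. That stands too.

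That the entry form contains DCS and knowledge is an inference from the statement that the questionnaires are filled in again; the Data collection section does not list their content.

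A reader might also take the whole remedy to be a change of analysis wording. For the baseline part it is not, because of the timing shown in step 5. As the plan is written, the unadjusted follow-up comparison is safer than adjusting for a score taken after allocation.

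Finally, covariate detail is often left to an analysis plan that is not shown. This carries less weight, because the article does not leave the method open: it names the tests.

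**Conclusion.** The point holds as a recommendation to improve efficiency. The article fixes analyses that ignore the stratification factor and make no stated use of the entry scores.

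The two omissions have different consequences. Leaving out baseline costs power: 81.5% against 85% to 98% at 200 per arm, and 74.9% against 79% to 96% at 170 per arm, for assumed correlations of 0.3 to 0.7. Leaving out center makes standard errors conservative only if centers differ in outcome; under the assumed cesarean rates the chi-square's true level is about 4.3% to 4.5% (40% and 64%) or 3.2% to 3.5% (30% and 70%).

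The direction is secure for any nonzero correlation or real center difference. The size is not known from the documents. The center adjustment is justified without condition; the baseline adjustment only if the first questionnaire precedes knowledge of allocation and any contact with the decision aid.

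**What to change.** 1. **Center, unconditionally.** Analyze DCS and knowledge by linear models with arm and center. For delivery mode use a center-stratified Mantel-Haenszel test or logistic regression with arm and center. This changes analysis wording only.
2. **Baseline, conditionally.** Move the first questionnaire to the consent visit, before the envelope is opened, and confirm that it holds both scores. Then make the primary analysis an ANCOVA of the week-38 score on arm, center and the baseline value of the same outcome. The cost is a change in enrollment workflow at all four centers.
3. **If the questionnaire is not moved,** adjust for center only.
4. Put the same variables in the multiple imputation model and keep the t-test as a sensitivity analysis.
5. Fix these choices before outcome data are seen, so that covariates cannot be chosen on the results.

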## Background

Caesarian section rate in Iran is three times the global average rate. According to a report released by the Iranian Ministry of Health and Medical Education in 2005, caesarian sections constitute 40.7 % of all deliveries in Iran, including 52 % of the deliveries in Tehran (the capital of Iran), of which 64 % are performed in private hospitals [1]. Over the past 30 years, the rate of caesarian sections has been increased in a referral hospital in Tehran from 14.3 % in 1979 to 22.7 % in 1989, 52.5 % in 1999, and 85.3 % in 2009 [2].

A cross-sectional study on 824 pregnant women in Tehran, reported that 72 % of pregnancies with cesarean section were elective. Of these elective pregnancies, 22 % were performed because of a maternal request. Among pregnant women with these requests, 71 % had no explanation for their request. In addition, 65 % of doctors suggested cesarean delivery for their patients without a true medical indication [3]. Results of a study with 350 questionnaires filled out by pregnant women at waiting time for their prenatal visit in eight public health centers and four private offices in Mashhad, Iran, showed that 90 of these pregnant women (26 %) preferred cesarean delivery when a vaginal delivery was appropriate (unpublished observation). These findings are corroborated by studies showing that 70 % of pregnant women in Iran request cesarean section for reasons unrelated to health needs, such as physician's recommendation, personal request, and compliance to the spouse’s preference [4, 5].

Maternal request is one of the main reasons for increasing the rate of cesarean section in Iran. Cesarean delivery on maternal request (CDMR) is defined as the event in which a pregnant woman prefers and requests a cesarean delivery, without maternal or fetal indication, rather than proceeding with a plan for vaginal delivery [6].

The great variance in CDMR across countries suggests that women need help making a decision about the mode of delivery [6–8]. Gynecologists, midwives, and also the family, have significant effect on pregnant women’s decision on mode of delivery [7, 8]. As a result, the decision-making process may be hindered, for example, a disagreement between a physician and the family (unpublished observation).

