According to Orem's theory [28], decision-making constitutes a first phase of “deliberative self-care.” People who are competent at self-care and understand entirely the courses of actions are usually open to these actions and receptive to their effectiveness. Hence, improving the decision-making process by decision aids has the potential to enhance self-care. Informed decision-making can potentially reduce the over-use of expensive surgical procedures [29].

The objective of our overall project is to design, construct and evaluate a decision aid to help pregnant women choose mode of delivery. The system’s knowledge-base is obtained from the literature on cesarean delivery predictors. Our hypothesis in this study is that decision aid decreases decisional conflict and increases patient knowledge about cesarean and vaginal delivery modes. Decrease in the frequency of cesarean delivery on maternal request is a secondary expected outcome.

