### Sample size

We aim to detect absolute decrease of 15 % in the rate of decisional conflict between women in the intervention and control groups. A sample size of 400 pregnant women (200 per trial arm) is needed to detect this difference with a power of 80 % and 5 % risk of type I error. We used O’Connor’s Decisional Conflict Scaling method (0 to 100) to measure decisional conflict (or insecure feeling). The anticipated difference in outcome measure was based on a study assessing decisional conflict based on O’Connor's Decisional Conflict Scale of 212 Iranian pregnant women (mean 33.6; SD = 17.6) [8]. According to the O’Connor’s Scaling Method, decisional-aid tools are most effective when used for subjects with a score of 35 and above [25].

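### The comparison of delivery mode ignores each woman's recorded choice before the intervention; stratifying by it would recover power at almost no cost

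*Protocol article*

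**What the plan says.** The Background of the protocol article ends with the aims: "Decrease in the frequency of cesarean delivery on maternal request is a secondary expected outcome". The Discussion adds that requests for cesarean are expected to fall.

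The between-arm test that bears on this aim is in Statistical analysis. Actual mode of delivery is taken from hospital records and "differences will be tested by the Chi square test". No stratification or adjustment is stated.

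Under Outcome, the investigators will determine the women's "decision on mode of delivery before and after intervention and compare the results with the actual delivery mode". That is a comparison of stated with actual mode, and no use of the entry decision in the comparison of arms is given. Emergency deliveries are reported but not evaluated.

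The inclusion and exclusion criteria do not select on preference. They do exclude women whose mode of delivery is already fixed on clinical grounds. On how common the preference is, the Background cites an unpublished survey of 350 women in the same city: "90 of these pregnant women (26 %) preferred cesarean delivery when a vaginal delivery was appropriate".

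On timing, Data collection places the first questionnaire at study entry. Study design describes the order: consent, envelopes opened at the university, women phoned according to their arm, and only then an invitation to fill in the questionnaires.

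**The concern.** A woman's choice at entry is likely to be the best single predictor of how she delivers, short of a clinical indication. A test that leaves it out carries avoidable noise. If the aid acts mainly by changing the minds of women who want a cesarean, and these are a minority, the difference between whole arms is only a fraction of the change in that minority.

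At stake is the reading of the secondary result. A moderate change among women who prefer cesarean could leave the pooled comparison non-significant, and such a result might be taken as evidence that the aid does not affect delivery choice. The protocol already plans to collect the variable that would sharpen the comparison.

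**Working it through.** **The plan's own figure.** The Sample size section gives 200 per arm for decisional conflict ("We aim to detect absolute decrease of 15 % in the rate of decisional conflict"; "mean 33.6; SD = 17.6"). Reading 15% as relative to the mean gives 0.15 × 33.6 = 5.04 points. With SD 17.6 and two-sided 5%, that needs 192 per arm for 80% power, and 200 per arm gives 81.7%. So 200 is about right on that reading (the word absolute does not fit it, which is a separate matter). No effect size or power is given for mode of delivery.

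**Inputs for delivery mode.**
- From the documents: n = 200 per arm; 90/350 = 25.7%, printed as 26%, preferring cesarean.
- Assumed: 26% applies to this trial, so 0.26 × 200 = 52 women per arm prefer cesarean and 148 do not; two-sided 5%; 85% of the 52 control women deliver by cesarean against 60% of the 52 intervention women; background cesarean b in the other women is equal in both arms, from 5% to 30%; all women are analysed.

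**Pooled rates.** Control = 0.26 × 0.85 + 0.74b; intervention = 0.26 × 0.60 + 0.74b. The difference is 0.26 × 0.25 = 0.065, so 25 points among preferring women become 6.5 points overall (1/0.26 ≈ 3.8, about fourfold).

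**Power of the plain test.** Power = Φ{[d − 1.96√(2p̄(1−p̄)/n)] / √[(p₁(1−p₁) + p₂(1−p₂))/n]}, where d = p₁ − p₂ and p̄ is the mean of p₁ and p₂.
- b = 5%: 25.8% v 19.3%. (0.065 − 1.96 × 0.0418)/0.0417 = −0.41, power 34%.
- b = 30%: 44.3% v 37.8%. (0.065 − 1.96 × 0.0492)/0.0491 = −0.64, power 26%.

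**A larger effect.** If half of the preferring women change (85% v 42.5%), d = 0.26 × 0.425 = 0.1105. Power is about 79% at b = 5%, 70% at 15% and 62% at 30%.

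**Stratified by entry preference** (Mantel-Haenszel, simulated, same assumptions):

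| Scenario | Plain | Stratified |
|---|---|---|
| 85% v 60%, b = 5% | 34–35% | 60% |
| 85% v 60%, b = 30% | 26% | 29% |
| 85% v 60%, and the aid also lowers b from 15% to 10% | 62% | 80% |

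The gain is large when entry preference separates the women well (85% v 5%) and small when it does not (85% v 30%). Stratifying did better in each case.

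**Within preferring women only.** 85% v 60% with 52 per arm gives about 82%. With 45 per arm, for example after emergency deliveries are set aside, it is about 77%. At 80% v 60% with 52 per arm it is about 61%.

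**Sensitivity to the 26%.** For 85% v 60%, pooled power is about 52–57% if 40% prefer cesarean, about 71–73% if 50% do, and about 94% if 70% do.

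**The case against.** A reader might infer that most of the sample cannot show the effect. The documents do not support that. Women enter from 28 weeks and are asked again at 38 weeks, and the Background says that clinicians and family weigh heavily on the choice. Undecided or vaginally inclined women could move towards a request, and the aid might prevent this. If it did, with b falling from 15% to 10%, pooled power would be about 62% rather than 29%.

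A reader might also infer that a real benefit will probably be missed. That depends on an effect size the protocol does not give. At 85% v 60% it is true; if half of the preferring women change, it is not. Nor is 26% this trial's baseline. It comes from another sample, while the trial sites were chosen for readiness and the participants must read, write and use a computer. The Background also cites 70% of women requesting cesarean for non-health reasons. The meaning of that figure is unclear, but a higher share would mean much less dilution.

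A third temptation is to make the preferring women the lead analysis. That would rest on about 104 women, narrow the question and drop any effect in the rest. The all-women comparison validly estimates the effect of offering the aid to this population.

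Finally, the outcome is secondary, the trial was not sized for it, and supplementary analyses are often left to an analysis plan. Low power for a secondary outcome is not in itself an error, and nothing in the protocol says a null result would be over-read. All this stands. It limits the size of the point but does not defend the choice of test: the article names an unadjusted test while planning to record a strong predictor.

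**Conclusion.** The point holds as an inefficiency in a secondary analysis. It is not a flaw in the primary comparison. The plain chi-square leaves out the choice recorded before the intervention. Under the assumptions shown, it has roughly one chance in three or fewer of detecting a moderate effect confined to women who prefer cesarean. Stratification improves on it by an amount that depends on how well preference predicts delivery. That strength is assumed here, since the protocol gives no figure for it.

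The timing in Study design adds a condition. As described, the questionnaires are completed after women know their arm. If the entry decision is recorded there, it is not a clean baseline, and in an unblinded trial the strata themselves could be affected by allocation.

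**What to change.** - Replace the plain chi-square on delivery mode with an all-women between-arm comparison stratified by entry preference (Mantel-Haenszel), or a logistic model with arm and entry preference.
- Prespecify the between-arm comparison among women who prefer cesarean at entry as supportive, not as the lead analysis.
- Record entry preference at consent, before the envelope is opened, and say so in Study design and Data collection.
- State that a null all-women result will not be read as showing that the aid has no effect on delivery choice.

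The cost is one added item at enrolment, which changes the clinic workflow slightly, and a little more analysis. No additional women are needed.
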